**D. Data Analysis and Power Analysis:**

Outcome Measures: The following outcome measures will be used in this study. All questions will be asked at baseline, midpoint and endpoint with the exception of IBS-Global Improvement Scale (IBS-GIS) and IBS-Adequate Relief (IBS-AR).

IBS Global Improvement Scale (IBS-GIS): “Compared to the way you felt before you entered the study, have your IBS symptoms over the past 7 days been: 1) “Substantially Worse”, 2)”Moderately Worse, 3)”Slightly Worse”, 4)”No Change”, 5) ”Slightly Improved”, 6)”Moderately Improved” or 7) “Substantially Improved” (Kellow, 2003, Lembo, 2001; Gordon, 2003). A responder was defined as a patient who answered that their symptoms were either “moderately improved” or “substantially improved”. This will be our primary outcome.

IBS Global Symptom Assessment (IBS-GSA): Overall IBS symptoms will be rated by the subject by answering the following global question at the end of each week: Before you started taking the study “medication,” you said that you had [answer (in words) to baseline question 1 will be inserted here]. Compared to how you felt then, how would you rate your overall IBS symptoms during the past week? Possible answers are one of the following: Significantly relieved (+3);

Moderately relieved (+2); A little bit relieved (+1); Unchanged (0); A little bit worse (-1); Moderately worse (-2); Significantly worse (-3).

IBS Adequate Relief: Have you had adequate relief of your IBS symptoms over the past week? Yes or no

IBS Symptom Severity Scale (IBSSSS): The IBS Symptom Severity Scale (IBS-SSS) contains five questions that measure on a 100-point VAS, the severity of abdominal pain, the frequency of abdominal pain, the severity of abdominal distention, dissatisfaction with bowel habits, and interference with quality of life (Francis, 1997). All five components contribute to the score equally yielding a theoretical range of 0-500, with a higher score indicating worse condition. Previous studies have established that scores below 175 represent mild IBS symptoms, 175–300 represents moderate severity, and scores above 300 represent severe IBS (Francis, 1997). The total severity score on the IBS-SSS was treated as the gold standard measure of IBS severity. In the study by Francis et al., a decrease of 50 points correlatedwith improvement in clinical symptoms and was therefore considered to be a responder.

Abdominal pain/discomfort: Please rate the severity of your abdominal pain or discomfort (0-100)

Feelings of bloating and/or abdominal distention: Please rate the severity of your abdominal bloating or distention over the past week (0-100)

Relief of bloating and/or abdominal distention will be rated by the subject by answering the following question at the end of each week with “Yes” or “No”:

Have you experienced adequate relief of your feelings of bloating and/or abdominal distention during the past week? Additionally, patients will be asked to rate the severity of their abdominal bloating (0-100 scale).

Frequency of bowel movements: Patients will be asked to indicate the average number of bowel movement per day over the past week.

Quality of life questionnaire – specific for IBS (IBS-QoL) The IBS-QoL questionnaire consists of 34 individual questions. The response to each individual question is “not at all”, “slightly”, ”moderately”, “quite a bit”, or “extremely” (alternatively, questions 3, 5-7, 11, 14-15, 17-24, and 30-33 use a response of “a great deal” instead of “extremely”). The response is scored from 1 to 5, where 1 represents “not at all” and 5 represents “extremely / a great deal”. Eight domain scores (i.e. dysphoria, interference with activity, body image, health worry, food avoidance, social reaction, sexual, and relationship) and an overall score are derived from the 34 individual item scores.

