**Planned Statistical Analyses**

For continuous measures (i.e., IBS-SSS and IBS-QoL), we will conduct analyses of covariance (ANCOVA) controlling for baseline scores to test whether the open-label placebo yields a significantly greater benefit at the three-week endpoint than any improvement occurring in the wait-list control. For categorical measures (i.e., IBS-GIS, IBS-AR), we will conduct chi square tests to determine whether the proportion of responders in the open-label placebo condition significantly exceeds the proportion of responders in the wait-list control. All tests will be two-tailed with alpha set at .05.

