**G. Subject Selection**

| **Subject Selection:**  Patients will be recruited from the BIDMC GI Clinic and through IRB approved advertisements.  **Inclusion/Exclusion Criteria:**  Inclusion Criteria:   1. Only adults (>18 years of age) meeting the Rome III Criteria for IBS will be eligible for entry into the study. 2. Patients with ‘warning symptoms’ (e.g., unexplained weight loss, family history of colon cancer or inflammatory bowel disease, and rectal bleeding) will be required to have had a detailed workup to exclude organic pathology prior to enrolling the patient. 3. Participants will be allowed to continue their IBS medications (e.g., fiber, anti-spasmodics, antidepressants, loperamide, etc.) as long as they had been on stable doses for at least 30 days prior to entering the study and agreed not to change medications or dosages during the trial. 4. Patients will be asked not to make significant changes to their diet during the study. 5. In addition, patients will be required to have active symptoms at the entry of the study as defined by having an IBSSSS score of >150 (0-500 scale).   Exclusion Criteria:   1. Patients will be excluded if they had abdominal surgeries (excluding cholecystectomy, appendectomy, hysterectomy, and hernia repair). 2. History of inflammatory bowel disease (e.g., ulcerative colitis, Crohn’s disease). 3. Recent antibiotic use (within 1 month). 4. Radiation proctitis or other known poorly controlled medical conditions that could interfere with bowel function. 5. Patients will be excluded if they on narcotics or other pain medications (except for non-steroidal anti-inflammatory drugs). 6. Patients will also be required to have active symptoms at the time of entry into the study (score of >150 on the IBS-SSS). 7. Previous experience participating in randomized controlled trials for IBS. |
| --- |

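### Adequate relief (IBS-AR) asks about a current state but is not taken at baseline, so an IBS-AR responder need not be a patient who improved (minor; not the primary outcome)

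*Protocol*

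**What the plan says.** All references are to the protocol.

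- **Schedule** (Data Analysis and Power Analysis, Outcome Measures): "All questions will be asked at baseline, midpoint and endpoint with the exception of IBS-Global Improvement Scale (IBS-GIS) and IBS-Adequate Relief (IBS-AR"). The sentence does not say when the two excepted items are asked. The natural reading is that neither is asked at baseline.
- **IBS-GIS**, the primary outcome, is anchored to entry: "Compared to the way you felt before you entered the study, have your IBS symptoms over the past 7 days been", followed by a seven-point scale from worse to improved.
- **IBS-AR** has no such anchor: "Have you had adequate relief of your IBS symptoms over the past week? Yes or no".
- **Eligibility** (section G): "patients will be required to have active symptoms at the entry of the study as defined by having an IBSSSS score of >150" on a 0–500 scale. No criterion concerns adequate relief. Background treatment may go on: "Participants will be allowed to continue their IBS medications", provided doses were stable for 30 days. The protocol's own severity bands are "scores below 175 represent mild IBS symptoms, 175–300 represents moderate severity, and scores above 300 represent severe IBS", so scores from just above 150 up to 175 enter as mild.
- **Analysis** (Planned Statistical Analyses): "For categorical measures (i.e., IBS-GIS, IBS-AR), we will conduct chi square tests to determine whether the proportion of responders" is higher on open-label placebo than on the wait-list. No baseline term is included. The continuous measures, IBS-SSS and IBS-QoL, are analysed by ANCOVA with the baseline score as covariate.

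**The concern.** The two excepted items differ in kind. A change item cannot be asked at entry; a state item can. Without a baseline answer, a yes on IBS-AR at week 3 mixes two groups: patients who gained relief during the trial, and patients who had it on their existing regimen and kept it. The hypothesis is about the first group only.

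Two things are at stake, both limited to IBS-AR. One is interpretation. The team's earlier IBS trial is reported in the protocol on adequate relief (62% versus 28%), and this trial is meant to supply preliminary data for a larger grant, so the IBS-AR rate is likely to be quoted and reused. The other is precision. Relief at entry probably predicts relief at week 3, and a strong predictor that is never recorded cannot be used to reduce the variance of the comparison. A later analysis plan cannot recover an answer that was not collected.

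**Working it through.** **No plan figure to reproduce.** The Statistical Power section gives power for t-tests on standardised differences only. It gives none for IBS-AR, and no document gives the share of patients relieved at entry.

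**Inputs**
- 40 per arm (Overall Design); two-sided alpha 0.05 (Planned Statistical Analyses).
- 62% and 28% adequate relief on augmented sham acupuncture and wait-list in the team's earlier trial (Placebo Responses in IBS). Carrying these over to open-label pills is an assumption.
- q, the share relieved at entry: assumed 5% to 25%.
- r, the proportion of those who stay relieved: assumed 90%, equal in both arms.

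**Method.** The unadjusted test is the Pearson chi-square without continuity correction. At q = 0, exact enumeration gives 88.8% power. The stratified test is Mantel-Haenszel over the two baseline IBS-AR strata, without continuity correction. With m₁ and m₂ patients per arm in a stratum, N = m₁ + m₂, t responders in total and a responders on placebo, the statistic is [Σ(a − m₁t/N)]² / Σ[m₁m₂t(N − t)/(N²(N − 1))]. Power for q above 0 comes from 200,000 simulated trials per row.

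**Reading A: 62% and 28% apply to patients not relieved at entry.** Each arm's rate is p = qr + (1 − q)p₀, so the difference is (1 − q) × 34 points whatever r is.

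| q | Placebo | Wait-list | Difference (points) | Unadjusted power | Stratified power | Gain (points) |
|---|---|---|---|---|---|---|
| 5% | 63.4% | 31.1% | 32.3 | 85% | 85% | 0.2 |
| 10% | 64.8% | 34.2% | 30.6 | 81% | 83% | 1.5 |
| 15% | 66.2% | 37.3% | 28.9 | 76% | 79% | 2.9 |
| 25% | 69.0% | 43.5% | 25.5 | 66% | 72% | 6.0 |

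Example at q = 15%: placebo 0.15 × 0.90 + 0.85 × 0.62 = 0.662; wait-list 0.135 + 0.85 × 0.28 = 0.373.

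**Reading B: 62% and 28% are whole-group rates that already include anyone relieved at entry.** The arm rates stay at 62% and 28%, so unadjusted power does not depend on q. The rate among patients not relieved at entry is p₀ = (p − qr)/(1 − q).

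| q | Placebo p₀ | Wait-list p₀ | Unadjusted power | Stratified power | Gain (points) |
|---|---|---|---|---|---|
| 5% | 60.5% | 24.7% | 89% | 89% | 0.6 |
| 10% | 58.9% | 21.1% | 89% | 91% | 2.2 |
| 15% | 57.1% | 17.1% | 89% | 93% | 3.9 |
| 25% | 52.7% | 7.3% | 89% | 97% | 7.8 |

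**Chance imbalance.** At q = 15% the arms differ by four or more already-relieved patients (4/40 = 10 points of response rate if all stay relieved) in about 27% of randomisations. The chi-square's standard error already allows for this, so it does not inflate the false-positive rate. It is part of the variance that stratification would remove.

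**The case against.** **The power loss depends on a reading.** A reader might infer from Reading A that the omission costs up to 23 points of power (89% to 66%). The documents do not support that. The background section gives 62% and 28% as rates in the trial's patients and says nothing about relief at entry. Its plain meaning is Reading B, under which unadjusted power stays at 89%. Even under Reading A most of the loss comes from enrolling relieved patients, which a baseline question does not undo. The size of this point is therefore the gain column. This objection stands.

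**The share is assumed.** It stands that q is unknown. Entry requires active symptoms, and the mild scores admitted are a narrow strip of a 500-point scale. Nothing in the protocol shows that 15% or 25% is realistic. Nothing excludes it either.

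**No bias, and not the primary outcome.** A reader might infer a biased comparison. Randomisation balances relief at entry in expectation, so there is none. IBS-GIS and the global symptom assessment are anchored to the pre-study state, and IBS-SSS and IBS-QoL are baseline-adjusted. Those outcomes answer whether patients improved.

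**Other covariates exist.** Baseline IBS-SSS, pain, bloating and IBS-QoL could partly stand in for a baseline IBS-AR answer, and covariate adjustment could be left to an analysis plan. This is true, but they are imperfect proxies and cannot identify who was relieved at entry.

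**The bloating item.** One might argue that the similar question, "Have you experienced adequate relief of your feelings of bloating and/or abdominal distention during the past week", is not excepted from baseline and so shows an inconsistency. This is weak. That item is scheduled weekly, and the global symptom assessment, which is change-anchored and also weekly, is not excepted either. The exception sentence is loosely drafted, and little can be built on what it leaves out.

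**Conclusion.** The point holds as a minor one, to be considered. IBS-AR is a state item grouped with a change item for the baseline exception. Entry does not exclude patients who already have relief, and the planned chi-square has no baseline term. An IBS-AR responder is therefore not necessarily a patient who improved, and a useful stratifier is not collected.

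The recoverable gain is about 0 to 6 points of power under Reading A and about 0.5 to 8 points under Reading B. Both ranges assume 5% to 25% relieved at entry, 90% of them staying relieved in both arms, the earlier trial's rates, and 40 per arm. At the low end of the share the gain is negligible, and the true share is unknown. The point also rests on reading the exception as no baseline assessment. If IBS-AR is in fact asked at baseline, only the analysis part remains.

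**What to change.** 1. In Outcome Measures, limit the baseline exception to items that ask about change, and state that IBS-AR is asked at baseline as well as at the follow-up visits.
2. In Planned Statistical Analyses, compare endpoint IBS-AR stratified by the baseline answer (Mantel-Haenszel), or in a logistic model adjusted for it, with all randomised patients included.
3. As a supplement, report the IBS-AR rate by arm among patients without adequate relief at entry.

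Eligibility, treatment, visits and sample size stay as they are. The cost is one yes/no question at an existing visit and a short addition to the analysis text. The supplementary rate is less precise than the whole-group one: at 15% relieved at entry it rests on about 40 × 0.85 = 34 patients per arm. It should therefore not replace the main IBS-AR comparison.

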#### F. DESCRIPTION OF RESEARCH PROTOCOL

#### Overview: This RCT seeks to determine whether non-deceptive (open-label) administration of placebo pill produces significantly more clinical improvement in IBS patients than an observation control.

#### Overall Design: Eighty patients with IBS will be randomized to a three-week course of either 1: non-deceptive open-label placebo pill in the context of positive expectation + usual care or 2. No treatment + usual care. Both groups will receive an equal amount of time with the practitioner. Patients will be assessed at baseline, mid-point and at the end of three weeks with the standard outcomes measures for IBS.

| Figure 1: Study Flow Chart  Open Label +usual care  (N=40)  No treatment waitlist+ usual care (N=40)  Baseline Evaluation and Randomization  (N=100)  Midpoint  Evaluation  Midpoint  Evaluation  3 Week Endpoint  Evaluation  3 Week Endpoint  Evaluation |
| --- |

Restatement of Research Question: A three-week course of non-deceptive open label placebo treatment will be produce statistically superior outcomes to a no treatment waitlist control group.

Design methodology and intervention:

Description of the non-deceptive placebo treatment arm: The intervention will

be geared to maximizing the contributions of positive expectation,

conditioning, adherence and a supportive and confident patient

practitioner relationship to the placebo response of IBS patients taking an

open-label placebo pill. The first phase of the discussion will be designed

to enhance expectation. Patients will be asked whether they have heard of

the placebo effect and what they think of it. After a brief exchange geared

to supporting any positive feelings the patient may have about placebo effects,

the practitioner will then talk about the evidence supporting the idea that just

taking placebo pills with a positive expectation initiates still poorly understood

effects that can have a profound impact of illness. It will be clearly explained that

placebo are made of "inert" substances like sugar pills but have been show

in clinical trials to improve patient symptoms. The practitioner will discuss

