**Mediation Analyses**

We also plan to conduct mediation analyses to determine whether any of the hypothesized mechanisms of the open-label placebo response (i.e., expectations, adherence, and the quality of the patient-practitioner relationship as measured by the WAI) can mediate the effects of experimental group assignment. For continuous variables (i.e., IBS-SSS and IBS-QoL), these analyses will take the form of analyses of covariance (ANCOVA), controlling for the influence of the mediators as well as the baseline symptom scores. For categorical outcome variables (i.e., IBS-AR, IBS-GSA, IBS-GIS) we will use logistic regression models. All analyses will be two tailed, with alpha set at .05. If the hypothesized mediators influence outcome, then the association between experimental group assignment (i.e., open-label placebo vs. wait list control) and outcome should significantly diminish or disappear altogether (in the case of complete mediation) once the mediators are added to the model.

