#### I. Possible Risks

| Safety Measurements  The safety of subjects will be monitored at each study visit  - AEs  -Vital signs and body weight  - Physical exam  - Concomitant medication use  *Risks:*  *Subjects may experience normal fluctuations in their IBS symptoms (i.e., abdominal pain or discomfort). But since no active treatment is being given and patients are being evaluated 3 times over 3 weeks by a practitioner experienced in IBS there is minimal risk to the patient.* |
| --- |

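### The IBS-GSA question is worded for pill-takers only, and its weekly timing (shared by the bloating-relief item) conflicts with the protocol's own assessment schedule

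*Protocol*

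**What the plan says.** In section D, Data Analysis and Power Analysis, under Outcome Measures, IBS-GSA has a single wording for every subject. It is completed "by answering the following global question at the end of each week: Before you started taking the study" medication (the protocol puts that last word in quotation marks itself). The patient's own baseline answer is then inserted, and the item continues: "Compared to how you felt then, how would you rate your overall IBS symptoms during the past week". Answers run from -3 to +3.

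The opening of the same section sets a general timing rule: "All questions will be asked at baseline, midpoint and endpoint with the exception of IBS-Global Improvement Scale (IBS-GIS) and IBS-Adequate Relief (IBS-AR"). IBS-GSA is not among the exceptions. The question on relief of bloating or distention, later in the same list, is also placed at the end of each week and is not excepted either.

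Overall Design in section F allocates half the patients to "No treatment + usual care" and states: "Patients will be assessed at baseline, mid-point and at the end of three weeks with the standard outcomes measures for IBS". Section I, Possible Risks, agrees: "patients are being evaluated 3 times over 3 weeks by a practitioner experienced in IBS".

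For analysis, Planned Statistical Analyses names IBS-SSS and IBS-QoL for ANCOVA, and IBS-GIS and IBS-AR for chi-square tests. IBS-GSA appears only under Mediation Analyses: "For categorical outcome variables (i.e., IBS-AR, IBS-GSA, IBS-GIS) we will use logistic regression models".

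**The concern.** There are two separate defects.

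The first is wording. Waitlist patients are asked to think back to the start of a study pill that they never receive. Patients know their arm and the outcome is their own report. The intervention is itself the suggestion attached to taking pills, and the control visits are meant to avoid raising positive expectation. In such a trial an outcome question should not mention the treatment to one arm and misdescribe the situation of the other. If the two arms read the question differently, part of a difference in scores could come from the question.

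The second is timing. Site staff cannot tell from the protocol whether IBS-GSA and the bloating-relief item are collected weekly or at the three assessments, and a rating that looks back to baseline cannot be given at baseline. If the form is built on one reading and the analysis on the other, the number and dates of the ratings will not match.

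**Working it through.** No published figure has to be reproduced here. The check is a comparison of text with simple counts.

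**Wording**

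- Patients affected: the flow chart in section F shows 40 on open-label placebo and 40 on the waitlist. 40 / 80 = 50% see an introductory clause that does not describe them.
- Control treatment: the description of the control arm has these patients continue their regular IBS regimen. No study pill is given.
- Alternative version: none is given for the waitlist. The protocol does write separate questions by arm elsewhere (the Short Qualitative Description Report), so an arm-specific form was within its practice.
- Neutral model: the primary item, IBS-GIS, asks for a comparison with how the patient felt before entering the study. That reference is true for all 80 patients.

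**Timing**

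| Source | Time points for IBS-GSA | Post-baseline ratings |
|---|---|---|
| The item's own text | ends of weeks 1, 2 and 3 | 3 |
| General rule (IBS-GSA not excepted) | baseline, midpoint, endpoint | 2, plus 1 at baseline |
| Overall Design; Possible Risks | three assessments in three weeks, the first at baseline | 3 - 1 = 2 occasions |

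- Three weekly ratings do not fit two post-baseline assessments. The protocol describes no diary or weekly contact that would supply the rest.
- The protocol does not give the day of the midpoint. Read literally it is 3 / 2 = 1.5 weeks, which is not the end of a week. Then only the week-3 rating falls on an assessment, and two of the three weekly ratings have no occasion. If the midpoint were placed at the end of week 1 or week 2, one of the three would still have none.
- At baseline, IBS-GSA needs an earlier answer to compare with, and none exists. The general rule nevertheless includes it there.
- The bloating-relief item asks only about the past week, so it could be answered at baseline. It shares the weekly-versus-assessment conflict but neither the baseline problem nor the wording problem.
- Both schedules apply in the same way to both arms.

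**Use in the analysis**

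- Between-arm tests: four outcomes are named (IBS-SSS, IBS-QoL, IBS-GIS, IBS-AR). IBS-GSA is not one of them.
- Mediation models: five outcomes are named (IBS-SSS, IBS-QoL, IBS-AR, IBS-GSA, IBS-GIS). IBS-GSA is one of the five, and one of the three categorical ones.

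**The case against.** The strongest reply is that the item supplies its own comparator. It plays back what the patient said at baseline and asks for a rating against that. A waitlist patient can therefore answer sensibly despite the odd lead-in, and the protocol's quotation marks around the word medication show that the term was used loosely. This largely stands. A reader might infer that half the patients have no valid reference point; the inserted baseline answer rules that out. What remains is that the lead-in still names a treatment only one arm receives.

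It can also be said that placebo patients take the pill twice a day and discuss it at visits, so one more mention adds little, and that open-label self-report affects every outcome here. That is fair, and it is why no size can be put on the effect. It is not a reason to keep a clause that is untrue for one arm when a neutral one stands in the same section. That controls might leave the item blank is possible, but nothing in the protocol shows it.

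A reader might further infer that the timing conflict means the arms are measured differently. It does not: the ambiguity is the same in both.

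Finally, IBS-GSA has seven levels and no stated responder cut, although logistic regression is planned. That is not an error on this evidence. The cut, or the choice of an ordinal logistic model, can be left to a statistical analysis plan, and the protocol's wording does not exclude an ordinal model. Nor do the documents give a reason to remove IBS-GSA from the mediation list.

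**Conclusion.** The point holds as two small, separate defects. The lead-in to IBS-GSA fits only the 40 placebo patients and not the 40 on the waitlist. The end-of-week timing of IBS-GSA and of the bloating-relief item cannot be followed together with the general timing rule and the three assessments, and IBS-GSA cannot be asked at baseline as that rule implies.

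The consequence is limited. The primary outcome, IBS-GIS, already uses a neutral anchor and is untouched. IBS-GSA has no named between-arm test, so the wording bears on a planned analysis only through the mediation models. The protocol gives no basis for sizing a bias and none is claimed. A reader might infer that the trial's main comparison is compromised; the documents do not support that.

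The conclusion assumes that the single IBS-GSA wording shown is the one given to both arms, and that there is no weekly collection beyond the three assessments described. It is worth correcting because the correction is nearly free.

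**What to change.** 1. Replace the introductory clause of IBS-GSA with the study-entry anchor already used for IBS-GIS, in both arms. The inserted baseline answer can stay.
2. Add IBS-GSA to the items not asked at baseline.
3. State one set of time points for IBS-GSA, midpoint and endpoint, and delete the end-of-week instruction.
4. Reconcile the end-of-week instruction for the bloating-relief item with the same schedule; otherwise the contradiction survives in the next item.

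The cost is one reworded questionnaire item and a few lines of schedule text before enrolment. Sample size, visits and the primary analysis do not change.
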